##### Cannabis Abuse Screening Test (CAST) [46]

A 6-item screening tool to identify problematic cannabis use, particularly among adolescents and young adults, focusing on consumption habits and related issues over the past 12 months.

##### Fagerström Test for Nicotine Dependence [47, 48]

A 6-item questionnaire assessing the level of nicotine dependence in smokers.

##### Defense Style Questionnaire-40 (DSQ-40) [49, 50]

A 40-item questionnaire measuring 20 defensive mechanisms divided into three distinct styles: mature, neurotic or immature defenses.

##### Resilience Scale for Adults (RSA) [51]

A 33-item instrument evaluating protective resilience factors among adults.

##### Multidimensional Scale of Perceived Social Support (MSPSS) [52]

A 12-item questionnaire designed to measure perception of support in the dimensions of family, friends and significant other.

#### Study 2

A semi-structured interview guide is designed as an exploratory approach. This choice reflects the limited and fragmented body of research on psychological practices within the context of the ML. This is also in accordance with the diversity of possible practices in psychology and the existing inequalities in terms of working conditions through MLs. The study aimed to understand the subjective representations and situated practices of psychologists. An inductive and open-ended approach was deemed more appropriate. This design allows for the emergence of unexpected themes while avoiding the imposition of theoretical frameworks that might not fully account for the specific institutional and clinical realities of this context [53].

#### Study 3

##### Childhood Trauma Questionnaire Short Form (CTQ-SF) [30, 31]

A 28-item instrument evaluating various types of childhood trauma, including emotional, physical and sexual abuse, and emotional and physical neglect. An additional item has been included in this scale assessing commercial child sexual exploitation.

##### Food Insecurity Experience Scale (FIES) [32–34]

An 8-item measure assessing the severity of food insecurity experienced, based on difficulties accessing adequate food.

##### Patient Health Questionnaire-9 (PHQ-9) [35, 36]

A 9-item tool used for depression screening that also provides an indication of the severity of depressive symptoms.

##### Generalized Anxiety Disorder (GAD-7) [37–39]

A 7-item self-report questionnaire designed to assess the patient’s anxiety levels over the previous two weeks.

##### International Trauma Questionnaire (ITQ) [40, 41]

An 18-item self-report measure of PTSD and CPTSD symptoms based on ICD-11 criteria. It includes clusters of PTSD, clusters of DSO and functional impairment for both clusters.

##### Defense Style Questionnaire-40 (DSQ-40) [46, 47]

A 40-item questionnaire measuring 20 defensive mechanisms divided into three distinct styles: mature, neurotic or immature defenses.

### Data analysis

#### Study 1

The statistical analyses of the cross-sectional study will be performed using R software (RStudio), applying a significance level of 0.05. Descriptive and multivariate analyses (e.g., Chi-square/Fisher’s exact tests, correlation tests, ANOVA, etc.) will be used to characterize the population. The research team will also conduct correlation and factor analyses. In addition, we intend to perform a network analysis [54]. We will refer to the STROBE guidelines for epidemiological studies [55].

### Study 2

The analysis of the data from the semi-structured interviews will be conducted following a CQR approach. The themes will be identified by two researchers, using a structured and iterative procedure, aimed at the systematic search for a consensus among researchers. A third researcher, external to the data analysis, will be responsible for validating the categories in order to minimize primary group biases. The process will follow COREQ-32 recommendations [56, 57]. NVivo 15 software will be used.

### Study 3

The primary analysis will be based on repeated-effects linear mixed models, allowing assessment of the evolution of scores over time while taking into account intra-individual correlation and the longitudinal structure of the data. The group x time interaction, defined a priori, will be tested with a two-sided significance threshold set at α = 0.05, without correction for multiple comparisons. In addition, the research team will conduct: intergroup comparisons at several times (Student’s t-tests), intra-group comparison between two time points (paired t-test), exploratory analyses of subgroups based on sociodemographic or biographical variables. If data distribution is non-parametric, analyses such as Mann-Whitney, Wilcoxon, and Kruskal-Wallis tests will be employed. To limit the risk of type I errors in secondary and post-hoc analyses, a significance threshold adjustment will be applied in cases of multiple comparisons, using a Bonferroni correction (corrected α = 0.05 / m, where m corresponds to the number of tests performed within the same set of hypotheses). Exploratory analyses will be clearly identified as such and interpreted with caution, given the sample size.

Missing data will be taken into account based on their nature and frequency. If their proportion exceeds 5%, multiple imputation may be considered to limit bias, subject to the identified non-response mechanism [58].

All statistical analyses will be performed using the R software (RStudio).

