## Method/design

This research project is designed around three distinct methodological approaches. These phases are complementary (see: Table 1).

A cross-sectional study (study 1) based on a quantitative approach, consisting of the widespread distribution of standardized online questionnaires and scales (see: Measures) to young adults receiving support from any ML nationwide.The instruments facilitate a systematic collection of quantitative data and a multidimensional analytical framework to model the associations between psychological and social vulnerability factors. This design supports the identification of overarching statistical patterns.A qualitative study (study 2) intended for psychologists within MLs. This exploratory study offers a complementary perspective on understanding the experiences of youth at the MLs. By collecting data through verbatim analysis this study helps to identify some of the individual and institutional issues that influence the dynamics of care in these structures.An interventional longitudinal study (study 3) comparing two support programs. It is a multicenter, two-arm, parallel-group, single-blind randomized controlled trial. Participation is voluntary for young people experiencing severe FI and psychological distress, with a history of ACE, exclusively from MLP. The control group receives weekly food assistance for 12 months. The experimental group benefits from an intervention combining weekly food assistance for 12 months and twice-monthly psychological follow-up for 6 months. The study follows a superiority framework, hypothesizing that the combined intervention (food assistance plus psychological support) will lead to greater improvements in psychological distress and FI level compared to food assistance alone.

*Participants are assessed 4 times (T0: start of the program*,* T1: 3 months after the beginning*,* T2: end of the psychological intervention (6 months after the beginning)*,* T3: end of the program (12 months after the beginning). Each assessment period allows for the measurement of changes over time through standardized scales and semi-structured qualitative interviews. Detailed analyses will enable comparison of the specific effects of each intervention.*

**Table 1 Tab1:** Summary table of the research methodology

	Study 1	Study 2	Study 3

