Recruitment: The longitudinal study is intended for young people from MLP. Young people will be recruited through an explanatory email and the distribution of a flyer in the 6 MLP. Young people who have expressed interest will be interviewed by a member of the research team to verify their eligibility (see: Table 1), provide them with a detailed information sheet (see: supplementary material), and answer any questions. Eligible persons will then have 15 days to consider their decision and formalize their participation by signing the informed consent form (see: supplementary material).Randomization procedure: Participants will be assigned to one of two arms using a single-blind randomization procedure (1:1 allocation ratio). The assignment will be handled by a researcher who will not perform the data analysis, using a computer and a random number generator. The sequence will be stored in a secure file until participant enrollment is completed. Due to the nature of the intervention, neither the participants nor the facilitators (partner psychologists) can be blinded to group membership. However, the analysts of the outcome data will remain blinded to this group membership during statistical analyses. No formal unblinding procedure is planned, as there is no blinding at the participant level.Intervention and comparator: The control group will receive food assistance once a week for 12 months. The experimental group will receive the same food aid and in addition, psychological support twice a month for 6 months. The psychological support consists of individual sessions conducted by experienced psychodynamic psychologists and partners of the MLP. Food aid consists of distributing food baskets from MLP partner associations. The services are already offered by the MLP and are simply being reorganized within the framework of the study. In order not to deprive participants of potential care, the comparison of these two distinct approaches was guided by strong ethical considerations.Assessments and outcomes: These conditions enable the effects of different types of interventions to be measured within a supportive framework. Each participant will have 4 evaluation times during the year (T0, T1, T2, T3). Each time, they will first complete standardized scales and then have a semi-structured interview (see: Fig. 1). The interview will aim to characterize the participant’s experience, gather information about their history (T0), and assess their adherence to the proposed follow-up care, living conditions, interpersonal relationships, and future projections (T1, T2, T3). A closing session (T3) will also allow for a retrospective evaluation of the experience of the program, the maintenance of its effects, and the desire to continue the follow-up care. The primary outcome is the change in food insecurity level between baseline (T0) to 12 months (T3). Secondary outcomes include: (1) change in depressive symptoms (PHQ-9 score), change in anxiety symptoms (GAD-7 score), change in PTSD and CPTSD symptom dimensions (ITQ criteria) and change in defensive functioning (DSQ-40 scores). Adherence to food assistance and/or psychological support and any change in participant situation will be documented based on self-report during semi-structured interviews.

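### The primary outcome is the T0-to-T3 change in food insecurity, but the primary test is a group-by-time interaction over four visits with neither the time coding nor the 12-month contrast named

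*Protocol article*

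**What the plan says.** The Study 3 part of Procedures fixes the endpoint: "The primary outcome is the change in food insecurity level between baseline (T0) to 12 months (T3"). The same section sets the visits: "Each participant will have 4 evaluation times during the year (T0, T1, T2, T3"). Method/design places T1 at "3 months after the beginning", T2 at the "end of the psychological intervention (6 months after the beginning") and T3 at the "end of the program (12 months after the beginning").

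For Study 3, the Data analysis section states that "The primary analysis will be based on repeated-effects linear mixed models", and then that "The group x time interaction, defined a priori, will be tested with a two-sided significance threshold set at α = 0.05". It gives no degrees of freedom, does not say whether time is a factor or a continuous variable, and names no visit or contrast. Between-arm t-tests at several visits are planned as additions to the primary analysis, and T3 is not singled out among them.

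Both arms receive the same weekly food aid for 12 months. The only component that differs, psychological support, lasts 6 months and so ends at T2, six months before the primary time point. The article declares a superiority framework in favour of the combined arm. It gives no power calculation, effect size or SD for Study 3.

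**The concern.** The endpoint is one number per arm comparison: how much more food insecurity changed by month 12. A group-by-time interaction over four visits can be at least three different tests, and only one of them is that number:

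- **Joint test, time as a factor:** it responds to any difference in change at T1, T2 or T3, in either direction.
- **Slope test, time as linear:** it compares straight-line trends over 0, 3, 6 and 12 months.
- **Group-by-T3 term, time as a factor with T0 as reference:** this is the between-arm difference in T0-to-T3 change.

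The design makes the choice matter. Because the differing component stops halfway, an effect that peaks at T2 and fades by T3 is a possible course, and it is the course on which the joint test and the 12-month contrast part company. At stake is what the trial may say about its primary outcome: a significant primary test need not mean a 12-month difference, and a real 12-month difference may be tested with less power than the data allow. An open coding also leaves the choice to be made after the data are seen.

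**Working it through.** **Plan's own figure.** Study 3 gives no power inputs, so there is nothing to reproduce beyond 35 + 35 = 70.

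**Inputs from the article.** n = 35 per arm; visits at 0, 3, 6 and 12 months; two-sided alpha 0.05.

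**Assumptions, not in the article.** Equal SD of 1 at each visit; compound-symmetric correlation rho = 0.4, 0.5, 0.6; complete data; between-arm differences d in SD units at T0/T1/T2/T3, with zero at T0 and positive values favouring the combined arm.

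**Formulas under compound symmetry.**
- Joint test: noncentral F with 3 and 66 df, lambda = n × SS / (2(1 − rho)), where SS is the sum of squared deviations of the four d values from their mean.
- Slope test: noncentral t with 68 df. Slope = sum of (t − 5.25)d / 78.75, and SE = sqrt(2(1 − rho) / (n × 78.75)). Here 5.25 is the mean visit month and 78.75 = 27.5625 + 5.0625 + 0.5625 + 45.5625.
- T3 contrast: noncentral t with 68 df, ncp = d(T3) / sqrt(4(1 − rho)/n).

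**Example, 0.3/0.6/0 at rho = 0.5.**
- Joint: mean of d = 0.225, SS = 0.2475, lambda = 35 × 0.2475 / 1 = 8.66, rejection 66%.
- Slope: (−2.25 × 0.3 + 0.75 × 0.6)/78.75 = −0.00286 per month; SE = 0.01905; ncp = −0.15; rejection 5.3%. The sign leans towards control although the early difference favours the combined arm.
- T3 contrast: ncp = 0, rejection 5.0%.

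**Example, flat 0.5/0.5/0.5 at rho = 0.5.**
- Slope: 0.5 × (−2.25 + 0.75 + 6.75)/78.75 = 0.0333; ncp = 1.75; power 41%.
- T3 contrast: ncp = 0.5 / 0.239 = 2.09; power 54%.

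**Rejection rates, rho 0.4 to 0.6.**

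| Difference at T1/T2/T3 (SD) | Joint, 3 df | Linear slope | T0-to-T3 contrast |
|---|---|---|---|
| 0/0/0 | 5% | 5% | 5% |
| 0.1/0.2/0 | 10-13% | 5.0% | 5% |
| 0.3/0.6/0 | 58-77% | 5.2-5.3% | 5% |
| 0.4/0.8/0 | 84-96% | 5.4-5.6% | 5% |
| 0.17/0.34/0.68 (linear in months) | 59-78% | 76-91% | 73-88% |
| 0.5/0.5/0.5 (early and held) | 45-64% | 35-49% | 47-64% |

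**Direction.** Lambda depends only on squares, so reversing every sign gives the same joint-test rates.

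**Wider check.** With rho from 0.3 to 0.7, both compound-symmetric and AR-type correlation, and 0.5 SD at T1 and T2 but none at T3, the joint test rejects in 41-89%, the slope test in 6-10% and the T3 contrast in 5%. At 0.8 SD the slope test reaches 8-18%. A simulation of 300 random-intercept mixed-model fits (0.5 SD at T1 and T2, compound symmetry, rho 0.5) gave 72% for the joint test, against 67% by formula.

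**The case against.** The strongest defence is that the two sections can be read together. In a model with categorical time and T0 as reference, the group-by-T3 interaction term is the between-arm difference in T0-to-T3 change. Procedures supplies the time point, Data analysis supplies the model, and a condensed article may leave coding to the full protocol or analysis plan. That reading is possible, but the article does not select it. It fixes the primary test, its threshold and its sidedness, and calls the test prespecified, while leaving out the one element that ties it to the endpoint.

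Several limits stand in full:

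- A reader might infer that the plan fixes an undirected 3-df test. It does not: no degrees of freedom are stated, and a linear-time test would have a sign.
- A reader might infer inflated type I error. With no effect at any visit, all three tests hold 5%. In the fading scenarios a true difference exists at T1 and T2. What goes wrong is its attribution to month 12.
- A reader might infer that the interaction is always the weaker test. The slope test beats the T3 contrast when the effect builds linearly (76-91% against 73-88%). The joint test about equals it for a flat effect under compound symmetry, and can exceed it under AR-type correlation.
- No single coding produces all the harms in the table.
- Large early effects on food insecurity that vanish by T3 are assumed. Both arms receive the same food aid, and the article gives no basis for 0.6 to 0.8 SD at T2.
- The superiority hypothesis in Method/design names no time point, and the additional t-tests could reveal an absent T3 difference.

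**Conclusion.** The concern holds as a mismatch between the stated endpoint and the stated test. The article promises an answer about the T0-to-T3 change and prespecifies a test that, as worded, need not give it. The size depends on a coding the article leaves open. Under a joint 3-df test, rejection with no 12-month difference runs from 10-13% for small early differences to 84-96% for large ones. Under linear time it stays at 5-6% for the same courses, and the cost is instead lost power when an early effect is held. These figures rest on equal SDs, compound symmetry at 0.4 to 0.6, complete data and assumed effect courses. The mismatch itself rests only on the text. The documents do not support saying that the trial's false-positive rate is inflated when there is no effect, or that the plan has committed itself to the joint test.

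**What to change.** In the Study 3 part of Data analysis, state that visit enters the mixed model as a four-level factor. State also that the single primary test is the 1-df between-arm difference in change in food insecurity from T0 to T3 estimated from that model, two-sided alpha 0.05, reported with its 95% CI. List the T1 and T2 contrasts and the overall interaction as secondary. The covariance structure can stay with the analysis plan, since the mismatch does not depend on it.

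The cost is one or two sentences, with no new data or visits. The statistical price is some loss of power if the true effect is linear in time (73-88% against 76-91% for the slope in the example above) or confined to T1 and T2. In the latter case there is no 12-month effect to find, and the secondary contrasts would show the early one.

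### Study 3 leaves unclear which secondary-score tests are Bonferroni-corrected, and by what divisor, while planning redundant visit and within-arm tests that can enlarge it

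*Protocol article*

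**What the plan says.** All references are to the Protocol article.

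- **Primary model (Data analysis, Study 3).** The primary analysis uses "repeated-effects linear mixed models, allowing assessment of the evolution of scores over time". No outcome is named. The group-by-time interaction "will be tested with a two-sided significance threshold set at α = 0.05, without correction for multiple comparisons".
- **Added tests (same paragraph).** The plan adds "intergroup comparisons at several times" by Student's t-test, paired t-tests within each arm between two time points, and exploratory subgroup analyses. The visits and pairs of visits are not fixed.
- **Correction (same paragraph).** Secondary and post-hoc analyses are adjusted where there are multiple comparisons, "using a Bonferroni correction (corrected α = 0.05 / m, where m corresponds to the number of tests performed". The sentence goes on to limit that count to tests belonging to one set of hypotheses. Neither the sets nor m are given.
- **Outcomes (Procedures, Study 3).** Change in food insecurity from T0 to T3 is the one primary outcome. Changes in PHQ-9, GAD-7, ITQ dimensions and DSQ-40 scores are secondary.
- **Hypothesis (Method/design).** Superiority is stated on two fronts: the combined intervention "will lead to greater improvements in psychological distress and FI level compared to food assistance alone".
- **Sample size (Participants, Study 3).** 35 per group, chosen pragmatically without a power calculation.

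**The concern.** Two error-control rules stand in one paragraph, and the text does not say where one stops and the other begins. An interaction test on PHQ-9 comes from the model called primary, which is uncorrected. It also concerns a secondary outcome, which is corrected. This matters because the Abstract and the Discussion place the expected benefit of the combined programme mainly in mental health, that is, in secondary outcomes. The choice of rule therefore decides how the expected effect is judged.

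The second problem is the divisor. A between-arm t-test at T1, T2 or T3 re-uses data already in the mixed model. A within-arm paired test does not estimate the randomised difference at all. Both can nevertheless count towards m. Since m is the number of tests performed in a set that is not defined, the threshold for a secondary claim depends on what the team later runs and how it groups the results.

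**Working it through.** The plan states no power or error-rate figure for Study 3, so there is none to reproduce.

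**Inputs from the article:** 35 per arm; four assessments; two-sided 0.05; four secondary instruments; three DSQ-40 styles. **Assumptions:** ITQ gives two scores (PTSD and DSO), so there are 1 + 1 + 2 + 3 = 7 secondary scores; effects of 0.5 and 0.8 SD; no dropout; a single-visit two-sample t-test.

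**Possible values of m**
- Three visit t-tests (T1, T2, T3) on one score form the set: m = 3.
- One between-arm test per secondary score: m = 7.
- All tests on one score: 1 interaction + 3 visit tests + 6 paired tests (three visits against T0, in two arms) = 10.
- All tests on all secondary scores in one set: 7 × 10 = 70.

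**Reading A: secondary interactions are corrected.** Power is P(T > t_crit), where T is noncentral t with 2 × 35 − 2 = 68 degrees of freedom and noncentrality d × √(35/2). That is 0.5 × 4.183 = 2.09, or 0.8 × 4.183 = 3.35. The critical value is taken at 0.05/m, two-sided.

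| m | alpha | t_crit | power, 0.5 SD | power, 0.8 SD | detectable at 80% power |
|---|---|---|---|---|---|
| 1 | 0.05 | 1.995 | 54.1% | 91.0% | 0.68 SD |
| 3 | 0.0167 | 2.455 | 36.5% | 81.1% | 0.79 SD |
| 7 | 0.0071 | 2.774 | 25.7% | 71.5% | 0.87 SD |
| 10 | 0.005 | 2.902 | 21.9% | 67.1% | 0.90 SD |
| 70 | 0.0007 | 3.546 | 8.4% | 43.0% | 1.05 SD |

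If 20% were lost (28 per arm, assumed), power at 0.8 SD would be 84% for m = 1 and 58% for m = 7.

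**Reading B: the uncorrected rule covers several scores.** Family-wise error for k independent tests is 1 − 0.95^k.
- k = 2 (food insecurity and one distress score): 1 − 0.9025 = 9.8%.
- k = 5 (FIES and one score per secondary instrument): 22.6%.
- k = 8 (FIES and seven secondary scores): 33.7%.

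Simulated with pairwise correlations from 0.3 to 0.7, these fall to 21–15% for k = 5 and 30–19% for k = 8. If only FIES is tested uncorrected, the rate is 5%.

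**Holm against Bonferroni on the same seven tests.** Holm compares the ordered p-values with 0.05/7, 0.05/6, and so on up to 0.05. Its first step equals Bonferroni and each later step is more lenient, so it never rejects less. In a simulation with correlation 0.5 and seven equal effects (assumed), average power per score rose from about 27% to 34% at 0.5 SD and from about 75% to 84% at 0.8 SD. A repeat using t-tests with 35 per arm gave 26% to 32% and 71% to 82%.

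**The case against.** **A primary-only reading is open.** A reader might infer that the plan leaves the interaction uncorrected on every score. The documents do not say so. The uncorrected test belongs to the primary analysis, there is one primary outcome, and secondary analyses are adjusted in the same paragraph. The plural "scores" could also mean one scale measured repeatedly. This part of the objection stands: the defect is ambiguity, not a stated uncorrected test of everything.

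**The correction works per family.** A reader might take m = 70 as the plan's divisor. The sentence limits m to one set of hypotheses, so 70 is only the extreme case. This also stands.

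**The two consequences exclude each other.** Secondary interactions are either inside the Bonferroni family, which costs power, or outside it, which inflates error. It would be wrong to charge the plan with both 43% power and 34% error.

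**Bonferroni is valid, and the sample is small anyway.** Both are true. With no correction, 35 per arm gives only 54% power at 0.5 SD, so low power comes mainly from the sample size, which the article openly says was not based on a power calculation. But Holm's advantage does not vanish because its first step equals Bonferroni; the later steps give the gain shown above.

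**The detail may sit in an analysis plan that is not shown.** A full list of tests is not required of an article, and the article promises that exploratory analyses will be labelled and read with caution. What remains is that the rules it does state overlap and that its divisor follows the tests performed.

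**Conclusion.** The point holds in a limited form. The article does not settle whether interaction tests on secondary scores are corrected. Its superiority hypothesis names two outcomes where only one is primary. Its divisor is not fixed in advance and can be enlarged by tests that add no randomised comparison.

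Under the corrected reading, power at 0.8 SD ranges from 81% to 43% as m goes from 3 to 70, with the lower end only if all tests form one set. Under the uncorrected reading, family-wise error ranges from 9.8% to an upper figure of about 34%, and less with correlated scores. The power figures rest on assumed effect sizes, single-visit t-tests and no dropout; the planned mixed model could differ. The claim that no realistic effect could reach significance is not supported. The wording should be corrected before unblinded data are seen.

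**What to change.** 1. State that uncorrected two-sided 0.05 applies to one test only: the between-arm contrast at T3 on the single primary outcome, change in food insecurity. Align the superiority hypothesis with this, or say explicitly that its distress component is judged under the secondary rule.
2. List the secondary scores in advance, for example PHQ-9, GAD-7, ITQ PTSD, ITQ DSO and the three DSQ-40 styles. Test each once, by the model-based between-arm contrast at T3.
3. Replace Bonferroni by Holm over that fixed list. The family-wise protection is the same and power is never lower.
4. Report T1, T2 and within-arm results as estimates with confidence intervals and no significance claim, so that they do not enter m.

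The cost is a change of analysis wording, with no effect on data collection. The downside is fewer p-values for visit-specific and within-arm results.

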### Participants

#### Study 1

Cochran’s formula (Z² × p × (1-p) / E²) was applied to determine the required sample size. We based our calculations on a population size of 180,000 young people supported during the previous year (N-1). The margin of error was set at 5%, with a confidence level of 95%. The required sample size for this cross-sectional study is therefore 384 respondents.

#### Study 2

Our qualitative study will include a sample of 15 volunteer psychologists from MLs, which is a number suitable for the Consensual Qualitative Research (CQR) method. Nevertheless, inclusion will continue until data saturation is reached. We will consider data saturation to have been reached when the analysis of a new interview reveals no new themes.

#### Study 3

To our knowledge, our study is one of the first to explore this approach in a structured and longitudinal manner. Considering the lack of comparable studies among precarious young adults we have adopted a pragmatic approach instead of a power calculation. We aim to include a total of 70 volunteer participants, or 35 people in each group.

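### Study 3's missing-data rule rests on an undefined 5% trigger and a mechanism that data cannot fully identify; the imputation it allows would not reduce bias in the primary mixed model, while the planned t-tests stay exposed

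*Protocol article*

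**What the plan says.** All of this is in the protocol article.

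- **Primary analysis** (Data analysis, Study 3): "The primary analysis will be based on repeated-effects linear mixed models". The group-by-time interaction "will be tested with a two-sided significance threshold set at α = 0.05, without correction for multiple comparisons".
- **Further analyses** (same section): "intergroup comparisons at several times (Student’s t-tests), intra-group comparison between two time points (paired t-test").
- **Missing data** (same section): "Missing data will be taken into account based on their nature and frequency". The next sentence is the only specific rule: "If their proportion exceeds 5%, multiple imputation may be considered to limit bias, subject to the identified non-response mechanism". It does not say what the 5% is a proportion of, which analysis the imputation serves, or what the imputation assumes.
- **Size** (Participants, Study 3): "We aim to include a total of 70 volunteer participants, or 35 people in each group". No dropout allowance appears there, since "we have adopted a pragmatic approach instead of a power calculation".
- **Follow-up** (Procedures; Safety considerations; Data monitoring and management): there are four assessments, and the primary outcome is change in food insecurity from T0 to T3. Anyone who leaves the research interviews or the support programme is counted as lost to follow-up. Participation ends if an exclusion criterion arises. Data gathered before someone leaves are kept.

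**The concern.** The rule is stated, but it cannot be carried out as written, and it does not match the analyses it accompanies. An analyst has to decide what the 5% refers to, whether to impute once it is passed, and which mechanism has been identified. The last of these has no empirical answer for the distinction that matters, MAR against MNAR.

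The stated purpose is to limit bias. A likelihood-based mixed model fitted to all observed visits is already valid under MAR, and standard imputation makes the same assumption again. The t-tests are where MAR loss does damage, and the rule does not mention them.

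At stake is the 12-month comparison with 35 per arm. A report could say that imputation was used to limit bias when the primary estimate had not moved, and the reader would not learn how far the result depends on an untestable assumption.

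**Working it through.** The article gives no dropout, effect-size or SD figure for Study 3, so there is no stated figure to reproduce. The check has four parts.

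**1. When the trigger fires.** Inputs: 70 participants, 4 assessments each.
- By participants: 0.05 × 70 = 3.5, so the 4th person missing passes it.
- By planned assessments: 70 × 4 = 280 and 0.05 × 280 = 14, so the 15th missing assessment passes it.

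The text does not choose between these readings.

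**2. Imputation against the mixed model.** Simulation with 35 per arm, 4 visits and 1,000 runs per scenario. Assumed, because the article gives none of these: continuous outcome with SD 1, between-visit correlation 0.6, true T3 difference −0.50 SD, and a log-odds slope of dropout on outcome of 0 or ±1 per SD. The mixed model has unstructured covariance; imputation is sequential regression by arm with 20 imputations. Mean T3 differences:

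| Dropout type | Loss by T3 | Relation to outcome | Full data | Mixed model | Imputation | Completers |
|---|---|---|---|---|---|---|
| MAR | 20% | same in both arms | −0.514 | −0.518 | −0.518 | −0.520 |
| MAR | 20% | one arm only | −0.507 | −0.508 | −0.509 | −0.618 |
| MAR | 20% | opposite by arm | −0.505 | −0.502 | −0.504 | −0.727 |
| MAR | 30% | one arm only | −0.493 | −0.491 | −0.490 | −0.663 |
| MAR | 30% | opposite by arm | −0.498 | −0.500 | −0.498 | −0.833 |
| MNAR | 20% | same in both arms | −0.510 | −0.507 | −0.508 | −0.511 |
| MNAR | 20% | one arm only | −0.501 | −0.553 | −0.552 | −0.630 |
| MNAR | 20% | opposite by arm | −0.508 | −0.632 | −0.632 | −0.787 |
| MNAR | 30% | same in both arms | −0.507 | −0.507 | −0.509 | −0.504 |
| MNAR | 30% | one arm only | −0.507 | −0.605 | −0.607 | −0.717 |
| MNAR | 30% | opposite by arm | −0.486 | −0.671 | −0.671 | −0.894 |

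The mixed model and imputation differ by at most about 0.003 SD anywhere, including the 10% and 40% scenarios not shown. Under MNAR loss that differs by arm, both are off from the full-data value by:
- 20% loss: 0.553 − 0.501 = 0.052 and 0.632 − 0.508 = 0.124 SD.
- 30% loss: 0.605 − 0.507 = 0.098 and 0.671 − 0.486 = 0.185 SD.

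When the relation is the same in both arms, the contrast shows no material bias.

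**3. Completers.** A t-test without imputation uses only people with the visit or visits concerned. Under MAR with opposite relations by arm, the completer estimate is −0.727 at 20%, −0.833 at 30% and −0.946 at 40% loss, against −0.50. The paired within-arm change was not simulated.

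**4. A simpler bound.** If the dropouts in one arm differ by δ from what MAR predicts, bias = loss × δ. With assumed loss of 0.2 to 0.3 and δ of 0.5 to 1 SD, this runs from 0.2 × 0.5 = 0.10 to 0.3 × 1 = 0.30 SD. Together with part 2, the illustrative range is about 0.05 to 0.30 SD. For scale, the SE of a plain completer comparison is √(2/28) = 0.267 SD at 20% loss and √(2/24.5) = 0.286 SD at 30%. The planned model's SE is not this one.

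**The case against.** Several points on the other side are sound.

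- **Absence is not the finding.** This is a condensed article, and the full protocol or an analysis plan may contain an MNAR sensitivity analysis. That it is not mentioned here proves nothing. What stands is that the rule which *is* stated is badly fixed.
- **The 5% is set in advance.** A reader might infer that the threshold is picked after seeing the data. It is not; only the decision once it is passed is left open. Nor does the article give a dropout rate from which to say that the trigger is certain to fire.
- **Identified can be read loosely**, as judging a plausible mechanism from recorded information. The T1 to T3 interviews do document adherence and living conditions. On that reading the condition is cautious, and might even admit an MNAR-type imputation. But the text does not say so, and such a judgement still cannot separate MAR from MNAR.
- **Imputation is not useless.** It could repair the t-tests, and auxiliary variables can make MAR more credible. The rule names neither use, so the criticism is limited to standard imputation for the primary model.
- **Mitigation exists.** Reminders are sent and data already collected are retained. This reduces loss but does not settle how the remainder is handled.

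**Conclusion.** The point holds as a defect in a stated rule, of moderate weight. The trigger has no denominator, its consequence is optional, and its condition cannot be met in the sense that matters. Standard imputation does not limit bias in the primary mixed model, and the t-tests can mislead even under MAR when dropout relates to outcome differently in the two arms.

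That such differences could arise here is plausible from the article itself. Leaving the support programme counts as loss to follow-up, and only the experimental arm has psychological sessions to leave. Participation stops when an exclusion criterion arises; Table 1 lists regular psychiatric care among these, so a participant who worsens may leave before the worsening is measured.

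A reader might infer that the 12-month result *will* be biased, or quote an inflated error rate. With bias b, the two-sided rejection rate is Φ(−1.96 + b/SE) + Φ(−1.96 − b/SE). This gives 5.4% for b = 0.05 with SE 0.267, and 18.3% for b = 0.30 with SE 0.286. The documents support neither end: loss, shift and SE are all assumed, and equal MNAR loss in both arms produced no material bias. The 0.05 to 0.30 SD range is an illustration, and the simulated outcome is a generic continuous score, not the food insecurity scale.

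**What to change.** 1. Delete the 5% trigger and the condition about an identified mechanism.
2. State that the primary analysis is the mixed model on all randomised participants with all observed visits, valid under MAR, without imputation.
3. Take between-group contrasts at each visit and within-arm changes from that model, in place of t-tests on whoever attended.
4. Prespecify, whatever the amount missing, one sensitivity analysis of the T3 contrast: multiple imputation with delta adjustment, separate shifts by arm (for example 0 to 1 SD), reporting the shift at which the conclusion changes.

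If the full protocol or an analysis plan already contains item 4, the article's rule need only be aligned with it. The cost is a few sentences and one extra analysis, and possibly a conclusion that has to be stated less firmly.
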